### Objectives, hypotheses, and other study goals

*The objective* of the “mStress-IHD” trial is to assess the efficacy and cost-effectiveness of the mHealth intervention “mindfulHeart” compared to standard care (control group) in terms of reducing stress in patients with ischemic heart disease (IHD).

*Primary hypothesis*: We expect the intervention to be superior compared to standard care in terms of reducing stress at the end of treatment (T1).

*Secondary hypotheses*: We expect the intervention to be superior to standard care in terms of improving health-related quality of life, functional capacity, self-efficacy, general distress, and stress at follow-up assessment time points (T2-T5). Furthermore, we expect the intervention to be superior to standard care in terms of reducing depression and anxiety symptoms, anger, and perceived stress. We expect the intervention to be superior compared to standard care in terms of cost-effectiveness.

*Other study goals* are to evaluate treatment satisfaction, usability, and perceived usefulness of the mHealth intervention. Furthermore, the study aims to evaluate predictors of usage behavior, time to dropout, and actual usage behavior. Actual usage behavior will be analyzed in terms of its influence on other study outcomes in an explorative approach.

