### Sample size calculation

The sample size calculation was performed using the R-package “Superpower” [53]. The primary hypothesis is that the intervention is superior in terms of reducing stress compared to standard care (control group) at T1. To assess the efficacy of the intervention, an ANCOVA with the primary outcome variable at T1 as the criterion, the group variable (intervention vs. control group) as a between-subject factor, and the individual baseline levels at T0 as a covariate will be performed. A subsequent mixed ANOVA with the respective measurements (T0–T5) as a within-subject factor and the group variable (intervention vs. control group) as a between-subject factor will then serve to explore the intervention’s effect at follow-up. For the sample size calculation, a preferred test power of 1-ß = 0.80 was chosen. We assume a moderate effect size of *d* = 0.5 for the baseline-adjusted comparison between the intervention and control group at T1. Furthermore, and based on previous studies [54], we expected the correlation between repeated measures to be *r* = 0.5. According to the power analyses, an effective sample size of *n* = 98 (i.e., 49 participants per group) would yield a statistical power of 80.34 for the above mentioned ANCOVA analysis. With the same amount of participants, we reach a power of 95.8 for the above-mentioned mixed ANOVA (given a rather conservative assumption of the sole difference between the intervention and control group to occur at T1). Based on existing literature regarding eHealth trials [55], we assume a dropout rate of 30%. Based on the preliminary work related to this study protocol [31, 32] and recommended measures to increase usability, especially user experience [55], a dropout rate in the lower level was assumed. Consequently, 128 participants (64 per group) are needed.

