### Statistical methods

The primary goal of this trial is to assess the efficacy of the intervention compared to the control group in terms of reducing stress directly after the intervention. For this purpose, an analysis of covariance (ANCOVA) with the outcome at T1, a between-subject factor (intervention group vs. control group), as well as the participants’ pre-intervention baseline values (T0) as a covariate will be used. The primary analysis will be performed in the intention-to-treat population, with missing data imputed in the case of dropout. Imputation will be calculated using the SPSS multiple imputation module with “monotone missing pattern” (as we will use complete data for sex, age, and baseline data of primary and secondary outcomes). The number of imputations will be set to 3000, and the seed will be set to the date of the analysis (ddmmyy). Interim analyses are not planned.

Subsequent mixed ANOVAs with a between-subject factor coding the group membership (intervention vs. control group) and a within-subject factor for the respective measurement (T0-T5) will serve to assess if the effect of the intervention is maintained at follow-up. Further clinical endpoints will be analyzed in a similar fashion. If, in any of the above-mentioned analyses, we find severe violations of normality or homoscedasticity, robust procedures (e.g., robust regression analyses, generalized estimating equations, or robust mixed linear models) will be used, instead. In case of violation of the sphericity assumption in the mixed ANOVA, appropriate corrections will be used (Huynh-Fieldt or Greenhouse–Geisser).

Treatment satisfaction, usability, and usage behavior will be analyzed descriptively. Furthermore, *t*-tests (or, in the case of a violation of the normality assumption, the Mann–Whitney *U*-test) and, for categorical variables, *χ*
^2^ tests (or, for variables with small cell sizes, Fisher’s exact tests) will be used to account for unlikely but possible differences in demographic and baseline parameters between the two groups. In addition, different groups (e.g., dropouts; group completing the intervention; group benefiting from the intervention) will be analyzed using analyses of variance and *χ*
^2^ tests to determine whether they differ from each other in terms of sociodemographic and clinical data.

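### The T0–T5 mixed ANOVA is given the question of whether the effect lasts, but its group-by-time interaction does not distinguish a lasting effect from one that is gone after T1

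*Protocol article*

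**What the plan says.** Among the secondary hypotheses, the protocol article expects the intervention to be superior to standard care on several outcomes "and stress at follow-up assessment time points (T2-T5") (Objectives, hypotheses, and other study goals).

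The analysis given to this question is a mixed ANOVA with group as the between-subject factor and "a within-subject factor for the respective measurement (T0-T5"). The Statistical methods section says that these ANOVAs "will serve to assess if the effect of the intervention is maintained at follow-up", and that further clinical endpoints are to be handled in a similar way.

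The Sample size calculation section says of this model: "With the same amount of participants, we reach a power of 95.8 for the above-mentioned mixed ANOVA". The figure is conditional: "given a rather conservative assumption of the sole difference between the intervention and control group to occur at T1". The other inputs are stated there too: "We assume a moderate effect size of *d* = 0.5 for the baseline-adjusted comparison" and "we expected the correlation between repeated measures to be *r* = 0.5".

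The article does not say which term of the mixed ANOVA carries the maintenance conclusion.

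**The concern.** The within-subject factor includes T0 and T1. At T0 randomization makes the expected group difference zero, and at T1 the trial expects its main effect. A difference at T1 alone is therefore enough to produce a group-by-time interaction, whatever happens at T2–T5. The scenario chosen to power the model is exactly that case: a difference at T1 and none afterwards. High power there means that the test usually rejects when no effect is left at follow-up.

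At stake is the secondary hypothesis of superiority on stress at T2–T5, and with it the article's aim of sustainable stress reduction. A transient benefit could be reported under an analysis described as assessing maintenance. The other clinical endpoints analysed in the same way share the problem. The primary T1 ANCOVA is not affected.

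**Working it through.** **Inputs** (Sample size calculation section): d = 0.5; one common correlation r = 0.5, which is compound symmetry; 49 evaluable per group; six time points. Alpha and sidedness are not stated; two-sided 0.05 is assumed.

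**The plan's own figures first**

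- ANCOVA at T1: noncentrality = d/√(1 − r²) × √(n/2) = 0.5/√0.75 × √24.5 = 2.86, with 2n − 3 = 95 degrees of freedom. Power is 80.8%, against the stated 80.34%. This reproduces.
- Mixed ANOVA, difference at T1 only: the interaction test below gives 68.2% at 49 per group, against the stated 95.8%. This does not reproduce. With 98 per group it gives 95.5%, so the stated figure may have used the total of 98 as the group size. That is a separate matter and does not alter this point.

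**Interaction test.** Let δ_t be the group difference at time t, in standard deviation units. The noncentrality is λ = (n/2) × Σ(δ_t − mean δ)² / (1 − r), with 5 and 5(2n − 2) = 480 degrees of freedom. Only the spread of the six differences around their mean enters.

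- Gone after T1, (0, 0.5, 0, 0, 0, 0): mean 0.0833; Σδ² = 0.25; spread = 0.25 − 6 × 0.0833² = 0.2083.
- Held to T5, (0, 0.5, 0.5, 0.5, 0.5, 0.5): mean 0.4167; Σδ² = 1.25; spread = 1.25 − 6 × 0.4167² = 0.2083.
- Linear fade over visits to zero at T5, (0, 0.5, 0.375, 0.25, 0.125, 0): mean 0.2083; Σδ² = 0.4688; spread = 0.4688 − 6 × 0.2083² = 0.2083.

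In all three cases λ = 24.5 × 0.2083 / 0.5 = 10.21, and power is 68.2%. In the first case a single point (T1) departs from the other five; in the second a single point (T0) departs from the other five. The test sees the same amount of variation.

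Partial persistence gives more power at 49 per group: 89.3% for an effect at T1–T2, 92.9% for T1–T3 and 89.3% for T1–T4. The T1-only scenario is therefore conservative relative to these, but not relative to full persistence, where the power is the same.

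**Group main effect of the same model.** λ = (n/2) × (mean δ)² / ((1 + 5r)/6), with 1 and 96 degrees of freedom, and (1 + 5 × 0.5)/6 = 0.5833.

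- Gone after T1: 24.5 × 0.0833² / 0.5833 = 0.29; power 8.3%.
- Held to T5: 24.5 × 0.4167² / 0.5833 = 7.29; power 76.2%.

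**Departure from a common correlation.** Simulation with 49 per group and 10,000 runs per scenario, transient against persistent effect:

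| Correlation | Uncorrected | Greenhouse–Geisser |
|---|---|---|
| Compound symmetry | 68.0% vs 67.5% | 66.9% vs 66.3% |
| AR(1) by visit | 47.5% vs 46.9% | 40.3% vs 40.4% |
| AR(1) by calendar time | 52.8% vs 50.5% | 44.5% vs 43.2% |

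A multivariate interaction test under AR(1) by visit gives 64.5% against 48.3%. It does separate the patterns, but with less power for the effect that lasts.

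**The case against.** The strongest reply is that the article never mentions the group-by-time interaction and never says that a significant one means the effect is maintained. The Sample size calculation section describes the follow-up model as exploratory and only reports its power under a stated scenario. Analysts would look at the means at T2–T5, and time-specific comparisons may stand in the statistical analysis plan, which is not shown. This reply holds against a reading that a reader might infer, namely that the plan would wrongly declare maintenance at a rate of 68% to 81% instead of 5%. That rate is the power to detect a real T1 difference. It becomes an error rate only if a significant interaction is taken as maintenance, and the upper figure (81.4% at 64 per group) also assumes that nobody drops out, whereas the protocol assumes 30%.

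Two further limits stand. Exact equality of power needs one common correlation; under AR(1) the univariate powers are only nearly equal. And it would go too far to say that the mixed ANOVA as a whole is blind to persistence, since its group main effect separates the patterns.

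The point nevertheless survives. The main effect averages in T0 and T1, so it does not show an effect at any follow-up visit. Nor can it be the term behind the stated power: under a T1-only difference it reaches 8.3% at 49 per group and 11.8% at 98 per group, far from 95.8%. Finally, this is more than a detail left to the analysis plan, because the article itself gives the question to a named model and powers that model on a case without maintenance.

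**Conclusion.** The point holds as a mismatch between a stated secondary question and the analysis assigned to it. Under the protocol's d = 0.5 and common r = 0.5, with two-sided alpha of 0.05 assumed, the omnibus interaction rejects with the same 68.2% probability at 49 per group whether the effect is gone after T1, fades linearly to zero at T5, or lasts to T5. A significant interaction therefore does not establish maintenance. If it were so read, a purely transient effect of d = 0.5 would be called maintained about 68% of the time with 49 evaluable per group. The size rests on compound symmetry and, for the persistent case, on a constant effect; under AR(1) the level is lower but the near-equality remains for the univariate test. The plan should be changed here, but the primary conclusion at T1 does not depend on it.

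**What to change.** Base both the maintenance conclusion and the T2–T5 superiority hypothesis on baseline-adjusted group contrasts at T2, T3, T4 and T5, estimated from one longitudinal model with T0 as covariate and T1–T5 as outcomes. Name in advance the contrast or contrasts that define maintenance; the key time point or testing order is for the sponsor to choose. Keep the omnibus group-by-time interaction as descriptive, and apply the same approach to the other clinical endpoints that now follow the mixed ANOVA.

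The Sample size calculation section should then no longer present power under a T1-only difference as support for the follow-up analysis.

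The cost is analysis work and wording only: Table 1 already schedules the combined stress measure at T0 through T5, so no visit or measurement is added.

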	**Planned assessment time points**				
**Measures**	**Baseline (T0–month 0)**	**During treatment** **(weekly assessment)**	**End of treatment (T1–month 3)**	**Follow-up 1–4 (T2–T5–months 4, 6, 9, 15)**	**Dropout**

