*Cost-effectiveness and cost-utility:* The objective of conducting an economic evaluation is to assess the cost-effectiveness of the intervention from an economic viewpoint. This evaluation will involve a cost-effectiveness analysis and a cost-utility analysis. To determine the cost-utility, quality-adjusted life years will be calculated based on the EQ-5D-5L questionnaire. The resource utilization will be evaluated by means of a questionnaire and will be measured in monetary units using the established standards of health economics. Furthermore, the costs per reduced unit of stress are assessed and compared between the intervention group and control group.
*Depression symptoms (BDI-II):* The BDI-II is a self-report questionnaire comprising 21 items that assess depression severity. Its reliability and validity have been established through various studies among diverse populations and cultural backgrounds. Higher scores indicate increased depression symptoms [41].
*Anxiety symptoms (STAI):* The STAI is the most authoritative tool for assessing anxiety in adults, precisely distinguishing between transient “state anxiety” and persistent “trait anxiety.” The STAI measures anxiety with 20 items and has a range of 20 to 80. A higher score indicates more pronounced anxiety [42].
*PROMIS-Anger Scale*: The PROMIS Anger scale comprises eight items that evaluate various aspects of anger. Scores on the scale range from 8 to 40, with higher scores indicating greater levels of anger [43].
*GHQ:* The GHQ assesses general distress and consists of 12 items. Respondents’ scores range from 0 to 36, where higher scores correspond to increased distress [44].
*PSS:* The PSS-10 item version is a short tool for the assessment of how individuals perceive stress in their lives. The values range from 0 to 40. Higher values indicate higher perceived stress [45].
*In-treatment assessments:* At the start of each intervention module (weekly), the following assessment instruments will be applied: Distress Thermometer (DT), Patient Health Questionnaire-4 (PHQ-4), and self-generated measures to assess coping skills and self-efficacy [46, 47].

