Furthermore, exploratory analyses including usage behavior and clinical outcome parameters (all assessments, including in-treatment assessments) will be conducted using, for example, different types of regression analyses. Time to dropout will be examined as a secondary endpoint, utilizing both the Kaplan–Meier estimate and the Cox proportional hazards regression.

Additionally, separate tabulations and line listings of adverse events and severe adverse events will be generated to thoroughly analyze safety.

To evaluate the cost-effectiveness of the intervention, the incremental cost-effectiveness ratio (ICER) and incremental cost-utility ratio (ICUR) will be calculated as the ratio of the mean cost difference and the mean difference in health effects (measured in terms of either stress (primary outcome) or QALY) between study groups during the follow-up period. The analysis will also consider the uncertainty of results.

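### The cost-utility analysis names no baseline covariate, so read literally the incremental QALY and cost give up precision that T0 data already collected would supply

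*Protocol article*

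**What the plan says.** The economic analysis is described in two places. Under Outcomes, the protocol says that "quality-adjusted life years will be calculated based on the EQ-5D-5L questionnaire". Under Statistical methods, the ICER and ICUR "will be calculated as the ratio of the mean cost difference and the mean difference in health effects", where the health effect is either stress or QALYs, compared "between study groups during the follow-up period". A further sentence promises that uncertainty will be considered. No covariate is named for the cost, QALY or stress difference.

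The same section is explicit about baseline for the primary outcome: the ANCOVA has the group factor, "as well as the participants’ pre-intervention baseline values (T0) as a covariate will be used".

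Table 1 schedules EQ-5D-5L at T0, T1 and T2 to T5. Health-care utilisation is recorded at T0 and T1 and, by its footnote, at months 6, 9 and 15. The section on randomisation and blinding specifies 1:1 blocks without stratification and takes balance of prognostic factors as an assumption.

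**The concern.** A patient's T0 utility is likely to predict the later utilities, and it is itself part of the QALY if the QALY is accumulated from T0. If arm means are simply subtracted, any chance T0 difference in utility carries into the incremental QALY. The same applies to costs if past utilisation predicts later utilisation. With 64 patients per arm and no stratification, some imbalance is to be expected.

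Cost-effectiveness is part of the trial's objective and one of its superiority hypotheses. The incremental QALY is the denominator of the ICUR, so noise in it affects the ratio strongly when the true difference is small. The plan uses the T0 covariate to gain power for efficacy but states no such gain for the economic comparison. The ICER could also end up with a different stress difference from the one reported as the primary result.

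**Working it through.** **1. The protocol's own figure.** The document gives no SD, precision or power for QALYs. Its one related figure is the power of the primary ANCOVA, 80.34% with 49 per arm. The inputs are "We assume a moderate effect size of *d* = 0.5 for the baseline-adjusted comparison" and "we expected the correlation between repeated measures to be *r* = 0.5". Two-sided alpha of 0.05 is assumed, because the text states none. With residual SD √(1 − 0.5²) = 0.866 and 95 degrees of freedom, the noncentral t gives 80.75%, so the figure is reproduced. Without the covariate, 49 per arm gives 68.8%. The efficacy analysis therefore depends on the baseline term.

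**2. QALY weights.** The visits fall at months 0, 3, 4, 6, 9 and 15 (Table 1). The trapezoid rule is assumed. In years:

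| Month | 0 | 3 | 4 | 6 | 9 | 15 | Sum |
|---|---|---|---|---|---|---|---|
| Weight | 0.125 | 0.167 | 0.125 | 0.208 | 0.375 | 0.250 | 1.25 |

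The squared weights sum to 0.3056.

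**3. Share of variance explained by T0 utility.** Take equal variances at all visits and a common correlation r. In utility-SD units:

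- Covariance of T0 utility with QALY = 0.125 + r × 1.125. At r = 0.5 this is 0.6875, which is also the slope of QALY on T0 utility.
- Variance of QALY = (1 − r) × 0.3056 + r × 1.25². At r = 0.5 this is 0.1528 + 0.7813 = 0.9340.
- R² = 0.6875² / 0.9340 = 0.506, a correlation of 0.711.
- Reduction in standard error = 1 − √(1 − 0.506) = 0.297.

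**4. Sensitivity.** The value r = 0.5 belongs to the stress outcome, and the document gives none for utility. It also does not say whether QALYs accumulate from T0 or from T1. From T1, the weights are 0.042, 0.125, 0.208, 0.375 and 0.250, with sum 1 and sum of squares 0.2639. At r = 0.5, R² = 0.5² / (0.5 × 0.2639 + 0.5) = 0.25 / 0.6319 = 0.396.

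| Assumption | R², from T0 | R², from T1 |
|---|---|---|
| Equal correlation, r = 0.3 | 0.31 | 0.19 |
| Equal correlation, r = 0.5 | 0.51 | 0.40 |
| Equal correlation, r = 0.8 | 0.80 | 0.75 |
| Correlation halves every 3 months | 0.20 | 0.06 |

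The last cell is covariance 0.177 and variance 0.495, so 0.177² / 0.495 = 0.06. It is the least favourable combination and lies below the 19% to 80% range of the equal-correlation rows.

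**5. Absolute scale.** This needs a utility SD, which the document does not give. Assume 0.20 (range 0.15 to 0.25), 64 per arm, r = 0.5 and accumulation from T0.

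- Standard error of the T0 difference = 0.20 × √(2/64) = 0.035.
- Shift in the incremental QALY from a T0 difference of that size = 0.6875 × 0.035 = 0.024 (range 0.018 to 0.030).
- Standard error of the incremental QALY = 0.20 × √0.9340 × √(2/64) = 0.034 unadjusted, and 0.034 × √(1 − 0.506) = 0.024 adjusted.

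No corresponding calculation is possible for costs, because the document offers nothing on their spread or correlation over time.

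**The case against.** The strongest reply is that the sentence is the usual definition of an ICER. It does not use the words raw or unadjusted, and a regression-adjusted mean difference would satisfy it. The article is condensed, and the analysis plan it mentions is not shown and may name the covariates. This stands in part: a reader might infer that the protocol commits to raw differences, and it does not say so. What remains is that the article states a calculation, leaves out the baseline term there, and includes it for the primary outcome. Anyone following the text literally would subtract arm means.

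Four further inferences are tempting and not supported:

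- **That the ICUR would be biased.** Under 1:1 randomisation the unadjusted difference is unbiased, and its sampling variance already contains chance imbalance. The issue is precision, and the particular imbalance that this trial happens to draw.
- **That half the precision is lost in any event.** The figure concerns variance, not the standard error, and it depends on the assumptions in the working.
- **That a T0 difference passes almost wholly into the QALY.** The slope is 0.69 against a maximum of 1.25, which is 55%.
- **That such a shift matches any plausible effect.** The document gives no expected QALY effect. Borrowing d = 0.5 with the assumed SD of 0.20, an effect sustained from T1 is 0.10 × 1.125 = 0.11 QALY, well above 0.024. An effect at T1 alone is 0.10 × 0.167 = 0.017, below it.

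The ICER may also need no change in substance. Its stress effect is labelled as the primary outcome, so the ANCOVA-adjusted difference may already be intended.

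**Conclusion.** The point stands as an improvement in precision and in protection against chance imbalance. It does not show an error or a bias. As written, the economic comparison has no baseline term, although the T0 measurements exist and the primary analysis uses its own. With r = 0.5, equal correlation at all lags and QALYs from T0 to T5, adjustment for T0 utility removes about 51% of the variance of the incremental QALY, or about 30% of its standard error. The gain is about 40% of the variance from T1 and about 20% with a correlation that halves every 3 months. It is 19% to 80% for equal correlations of 0.3 to 0.8, and only small if fast decay and a T1 start coincide. The gain for costs is unknown.

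**What to change.** In the cost-effectiveness paragraph of Statistical methods, state that:

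- the incremental QALY is estimated by regression on arm with T0 EQ-5D-5L utility as covariate;
- the incremental cost is estimated by regression on arm with T0 utilisation cost as covariate;
- the ICER uses the same baseline-adjusted stress difference as the primary ANCOVA;
- these adjusted estimates are the ones carried through the planned uncertainty analysis.

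If the analysis plan already says this, one clause in the protocol pointing to it is enough. The change costs a sentence or two. It adds no patients, visits or questionnaires, and it should be made before outcome data are seen, so that the choice between adjusted and unadjusted results is not left open.
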